### Study design

This study is a cluster RCT, with embedded economic and process evaluations. Schools are the unit of allocation because the intervention is school-wide. There will be two study sites, one in South West England and one in Wales, which will enable consideration of the generalizability of the findings.

In Wales, eligible schools will be drawn from two administrative areas (consortia) (*n* = 88), and within each area will be stratified into three levels according to FSM (high, medium and low). Two schools will be randomly selected from each stratum in each area, giving a total of 12 schools. A relevant senior manager in each school, e.g., a deputy head in charge of pastoral care, will be approached by the study team and their school invited to participate in the study. Any schools that decline will be replaced by a randomly selected school from the same stratum and geographical area.

In England, the study will be advertised by local public health teams to senior leaders and healthy schools contacts at all eligible schools within a 30 mile radius of one city (*n* = 64), and schools will then be followed up by the study team. Those who express interest in participating will be grouped by administrative area (city local authority [LA]/LA outside the city) and stratified into three levels according to FSM (high, medium and low). The aim will be to recruit two schools per stratum in each area, so if a stratum has more than two interested and eligible schools within the time frame, two will be randomly selected to give a total of 12 schools.

The sampling frame includes two administrative areas in each site to ensure a large enough sample is obtained. Schools will be stratified by area and FSM to ensure balance across study arms, in case administrative area or FSM status is associated with mental health outcomes. Including schools from different areas and with different levels of FSM eligibility will also help ensure the generalisability of the findings. If difficulties are encountered due to lack of interested or eligible schools in a particular stratum, two strata will be merged for that area. Table 1 shows the planned distribution of schools by strata, area and site.

**Table 1 Tab1:** Stratification of participating schools

		England		Wales	
		Area 1	Area 2	Area 3	Area 4
FSM eligibility (%)^a,b^	Low	2 schools	2 schools	2 schools	2 schools
		(range: 8.4–17.2)		(range: 3.8–15.3)	
	Medium	2 schools	2 schools	2 schools	2 schools

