### Intervention

The intervention has three elements:
**Staff peer support service:** all staff in the intervention schools will be invited to nominate colleagues whom they consider would make good peer supporters, via a confidential, anonymous written questionnaire. The one exclusion criterion for nomination will be membership of senior management, as pilot findings indicated that staff might feel uncomfortable using a support service that included senior leaders. The 8 % of staff with the most nominations - ensuring a mix of gender and teaching/non-teaching role by moving down the list until this mix has been met – will be invited to attend the 2 day standard MHFA training and to then set up a confidential peer support service for colleagues to access as and when required, with the aim of providing a listening ear and signposting to other services as appropriate. Anyone invited who does not want to do this will be replaced by the person matching their gender and role with the next highest number of nominations, and numbers of individuals not consenting to take part will be noted. The peer support service will be advertised through an initial awareness raising event and refresher one year later (see point 3), and also through posters, staff emails, and at staff meetings.
**MHFA for Schools and Colleges training for teachers:** A minimum of 8 % of all teaching staff (up to a maximum of 16) who have pastoral duties such as tutors or heads of year will receive this 1 day training, which is based on the youth MHFA course, but targeted to meet the needs of educational environments. Trained teachers will then continue with their usual teaching and pastoral roles within school, but will apply the MHFA for Schools learning in their day to day interactions with students; responding to signs and symptoms of distress and providing initial help and support to individuals they identify as at risk of mental health difficulties.
**Mental health awareness raising session for all teachers:** All teaching staff will receive a one hour awareness raising session, which will introduce the peer support service and focus on the importance of mental health issues in schools. A refresher session will be delivered at the start of the next academic year by the peer supporters themselves, to ensure that the profile of the peer support service is maintained.

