#### Mechanisms of change

Participants will be asked to rate stress and satisfaction at work, help provided and received at school, school’s attitude to staff and student wellbeing, and quality of relationships in school in the questionnaires, using Likert scales. Logistic regression models will be used to examine differences by study arm at follow up, adjusted for baseline scores, school-level FSM and geographical area. We will examine whether baseline measures of these variables moderate the effect of the intervention by including the appropriate terms in the analysis model – however this is purely an exploratory analysis as power will be low, and there is always the potential for unmeasured confounding of the association between moderator/mediator and outcome. We will also examine the extent to which the MHFA training appears to have impacted on mental health, wellbeing and helping behaviour. We will use a Complier Average Causal Effect (CACE) approach (using Instrumental Variable analysis or Principal Stratification) [48] to compare those who completed the training in the intervention schools with those in the control schools who would have completed the training, had they been offered it (based on matching their gender, role in the school and years of experience with those who were trained).

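### An instrumental-variable estimate of the MHFA training effect would break its exclusion restriction, because untrained teachers in intervention schools are also exposed to the intervention

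*Protocol article*

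**What the plan says.** The process evaluation (Mechanisms of change) states the aim: "We will also examine the extent to which the MHFA training appears to have impacted on mental health, wellbeing and helping behaviour". The method follows: "We will use a Complier Average Causal Effect (CACE) approach (using Instrumental Variable analysis or Principal Stratification". The purpose is to "compare those who completed the training in the intervention schools with those in the control schools who would have completed the training" had it been offered, the control teachers being identified "based on matching their gender, role in the school and years of experience with those who were trained".

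Two other sections bear on this. Study design says: "Schools are the unit of allocation because the intervention is school-wide". Intervention says: "All teaching staff will receive a one hour awareness raising session, which will introduce the peer support service", and the peer supporters are to "set up a confidential peer support service for colleagues to access as and when required".

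The Intervention section also describes two trained groups with different routes in. Peer supporters, who take the 2-day standard course, are the 8% of staff with the most nominations, mixed by gender and by teaching or non-teaching role. Trainees on the 1-day Schools and Colleges course are at least 8% of teaching staff, capped at 16, drawn from those with pastoral duties. The article does not discuss how the complier analysis would deal with the exposure of untrained teachers.

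**The concern.** An individual-level complier analysis with allocation as instrument needs two things. Allocation must not affect teachers who would not be trained, and it must affect those who would be trained only through their own training. The intervention is built so that neither holds. All teaching staff receive the awareness session, and the peer support service exists to help colleagues who were not trained.

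Under instrumental variables, or principal stratification that relies on the same restriction, any benefit to untrained teachers is credited to the trained minority and scaled up by the inverse of their share. A process analysis meant to show what the training did could then report a large training effect when the training itself did nothing.

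**Working it through.** **Inputs from the article**
- Teachers per school: about 60 (Study population).
- Peer supporters: 8% of staff; other trainees: at least 8% of teaching staff, at most 16 (Intervention).
- Target difference 3 WEMWBS points, SD 8.4, 12 + 12 schools, 50 teachers followed up per school, coefficient of variation of cluster size 0.5 (Sample size calculation).

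**1. The article's own figures.** It gives none for the complier analysis, only power for the primary comparison. The design effect is 1 + ((1 + 0.5²) × 50 − 1) × ICC.
- ICC 0.05: design effect 4.075, standard error 0.979, power 83.4% (two-sided 5% assumed, t with 22 df). The article states 83%.
- ICC 0.02: design effect 2.23, standard error 0.724, power 97.5% to 97.7%. The article states 98%.

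The power figures reproduce, and the 3 points and SD 8.4 are used below.

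**2. Share of teachers trained, p (assumed).** 8% of 60 is 4.8, so about 5 peer supporters and 5 to 16 other trainees:
- low: (5 + 5)/60 = 0.167
- high: (5 + 16)/60 = 0.35

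This takes all peer supporters to be teachers and nobody to be trained twice. The article gives neither the teaching/non-teaching split nor the overlap.

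**3. What each estimator returns.** Let s be the effect of being in an intervention school on every teacher, and tau the added effect of own training on the trained.
- Intention-to-treat difference = s + p × tau.
- Instrumental-variable estimate = (s + p × tau)/p = tau + s/p.
- Ideal matched contrast (trained against correctly identified would-be-trained controls) = tau + s.

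**4. Training does nothing (tau = 0) and s = 3.**
- Instrumental variable at p = 0.167: 3/0.167 = 18 points, or 18/8.4 = 2.1 SD.
- Instrumental variable at p = 0.35: 3/0.35 = 8.6 points, or 8.6/8.4 = 1.0 SD.
- Ideal matched contrast: 0 + 3 = 3 points.

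The true training effect is 0.

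**5. A smaller whole-school effect (tau = 0, s = 1).**
- Instrumental variable: 1/0.167 = 6.0 and 1/0.35 = 2.9 points.
- Ideal matched contrast: 1 point.

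**6. Simulation check** (24 schools of 50 teachers, SD 8.4, ICC 0.02, 2,000 runs, p = 0.16).
- s = 3, tau = 0: mean instrumental-variable estimate 19.0 (formula 3/0.16 = 18.75); matched contrast 3.0.
- s = 0, tau = 2: means 1.8 and 2.0. Both methods centre close to the truth when there is no whole-school effect, so the failure comes from s.

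**7. The matching set against the selection rules.** Pastoral role selects the Schools and Colleges trainees, and role is in the matching set. Colleague nomination selects the peer supporters. It is described only for intervention schools, and none of gender, role or years of experience stands in for it. The resulting bias cannot be sized from the article.

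**The case against.** The strongest reply is that the article names two methods, and that the contrast it goes on to define does not use untrained intervention teachers at all. That is right. If would-be completers in control schools are identified by covariates, nothing is divided by the share trained, and the 9 to 18 points do not apply.

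A reader might also infer that the bracketed matching is a fallback lying outside complier methods. The text does not support this. The matching is the stated way of finding would-be completers, and using baseline covariates for that purpose is a legitimate principal-stratum approach under an ignorability assumption. What can be questioned is whether three covariates make that assumption credible.

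Nor does the nomination argument reach everyone trained: by the counts above, 5 to 16 of the 10 to 21 trained teachers per school enter by pastoral role.

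It can further be said that this is a process analysis, cautiously worded, with details left to an analysis plan that is not shown. Its low weight is conceded. But the article itself fixes the aim, the candidate methods, the contrast and the matching variables. Its exploratory label is attached to the moderator analysis that comes before, and the caveats given there (low power, unmeasured confounding) do not cover an exclusion restriction known in advance to fail.

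**Conclusion.** The point holds for the instrumental-variable option and for exclusion-based principal stratification. With 17% to 35% of teachers trained, a 3-point whole-school effect and no training effect would be reported as about 18 to 9 WEMWBS points. The share trained is an assumption: a lower share, for instance if some of the 5 assumed peer supporters are non-teaching or some staff take both courses, would inflate the estimate more. The size of any whole-school effect is unknown; 3 points is used because the trial is powered for it.

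For the matched contrast the problem is smaller and different in kind. It estimates training plus whole-school exposure, not training alone, and for peer supporters it leaves out the nomination process.

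A reader might conclude that the whole analysis should be deleted in favour of a complier analysis at school level. That does not follow. A school that delivers only part of the package would count as a non-complier while still being treated, so exclusion could fail again, and the result would not answer the article's question about those who were trained. The primary intention-to-treat analysis and the power calculation are untouched.

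**What to change.** - Remove instrumental variables, and any principal stratification relying on the exclusion restriction, as options for this analysis.
- Keep the comparison of trained teachers with would-be-trained control teachers. State its estimand as the total effect of being a trained teacher in an intervention school, and label the result exploratory and observational.
- Add baseline WEMWBS, PHQ-8 and help provided to colleagues to gender, role and years of experience in the matching set. All three are in the planned teacher questionnaires.
- Analyse peer supporters and Schools and Colleges trainees separately, because they are selected differently.

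The change is to analysis wording and needs no new data. The cost is precision. With about 60 teachers in each of 12 intervention schools, the separate groups would have about 12 × 5 = 60 peer supporters and 12 × 5 = 60 to 12 × 16 = 192 other trainees, against 120 to 252 combined, before loss to follow-up.

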### Process evaluation

Informed by the Medical Research Council’s guidance [44], an embedded process evaluation will be conducted, using a combination of quantitative and qualitative methods. This will consider: mechanisms of change (see Fig. 1) and relevant contextual influences [45]; reach; contamination; intervention fidelity [46]; unintended harms [47]; acceptability; and sustainability.

Table 3 provides a summary of the ways in which the different process evaluation components will be assessed.

**Table 3 Tab3:** Process evaluation components and relevant data

Evaluation component	Relevant data
Mechanisms of change	*Teacher questionnaires* Stress at school Satisfaction at school Help provided to colleagues and students Help received from colleagues School’s attitude to staff and student wellbeing Quality of relationships in school *Student questionnaires* Help received from teachers School’s attitude to student wellbeing Quality of relationships with teachers *Interview with head teacher* Relevant new policies or practices introduced *Focus group with peer supporters* Nature of support provided *Focus groups with peer supporters and MHFA trainees* Learning from the MHFA training Application of learning Whether and how learning shared with colleagues *All focus groups (intervention)* Any perceived changes in school ethos or activities *Interview with peer support service users* Whether the service helped and how
Reach	*Teacher questionnaires* Use of the peer support service MHFA training completed *Termly peer supporter meetings* Record of how much help provided *Focus group with peer supporters* How service has been promoted *Focus group with students (intervention)* Perceptions of support from teachers and any changes
Contamination	*Focus group with teachers (control)* Any mental health training Any perceived changes in school ethos or activities *Focus group with students (control)* Perceptions of support from teachers and any changes *Audit of school activities* Any new activities in control schools similar to intervention
Intervention fidelity	*Focus groups with peer supporters and MHFA trainees* How much ALGEE model is used when supporting others Other MHFA techniques used when supporting others *Training observations* How well trainer sticks to core MHFA components *Interviews with trainers* Perceptions of MHFA core elements

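### Peer supporters are chosen by colleague nomination, which the planned matching of control counterparts ignores, so a matched or covariate-based CACE analysis could read selection as a training effect

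*Protocol article*

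**What the plan says.** In the protocol article, the Mechanisms of change part of the process evaluation sets out to examine "the extent to which the MHFA training appears to have impacted on mental health, wellbeing and helping behaviour". On method it says: "We will use a Complier Average Causal Effect (CACE) approach (using Instrumental Variable analysis or Principal Stratification". The stated aim is to "compare those who completed the training in the intervention schools with those in the control schools who would have completed the training" had it been offered, and those control staff are identified "based on matching their gender, role in the school and years of experience with those who were trained". No other variable is named for this purpose. The caution about unmeasured confounding in the same paragraph is attached to the moderator and mediator work, not to this comparison.

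The Intervention section describes two courses:

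- **2-day standard MHFA, followed by running the peer support service.** Here "all staff in the intervention schools will be invited to nominate colleagues whom they consider would make good peer supporters". Those invited are "The 8 % of staff with the most nominations", subject to a mix of gender and of teaching and non-teaching role. Anyone who declines is replaced by the next most nominated person of the same gender and role.
- **1-day MHFA for Schools and Colleges.** This goes to at least 8% of teaching staff, up to 16, who have pastoral duties. Nomination plays no part.

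No nomination exercise is described for control schools.

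**The concern.** A CACE analysis needs a credible account of who in the control arm would have been trained. For peer supporters, the replacement rule means that nomination rank decides among staff of the same gender and role. Gender and role are two of the three matching variables, so matching on them cannot stand in for nomination. Years of experience is at best a loose proxy.

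The outcomes of this analysis are mental health, wellbeing and helping behaviour. Being judged a good supporter by colleagues is plausibly related to all three. If it is, people picked for that quality would be set against ordinary colleagues of the same gender, role and experience, and a difference could appear although the training did nothing.

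The exposure is also unclear. One phrase, the MHFA training, has to cover two courses that differ in length, in selection and in what trainees do afterwards. A single estimate across both would describe neither. What is at stake is the trial's answer to whether the training itself changes those who receive it.

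**Working it through.** **1. The plan's own figure.** The protocol gives no size or power for this analysis. Its only power statement is for the primary comparison, and it reproduces. Inputs from Sample size calculation: difference 3 points, SD 8.4, mean 50 teachers followed up per school, coefficient of variation 0.5, 12 schools per arm, 5% level (taken as two-sided).

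- Design effect = 1 + ((0.5² + 1) × 50 − 1) × ICC, which is 4.075 at ICC 0.05 and 2.23 at ICC 0.02.
- Power with a t reference on 22 degrees of freedom is about 83% and 98%, as stated.

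The present point does not rest on this. It takes only the SD of 8.4 from there.

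**2. What decides selection, against what is matched.**

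| Course | Deciding criterion | Covered by gender, role and experience? |
|---|---|---|
| 2-day (peer supporters) | Nomination rank within gender and role | No, and not described for control schools |
| 1-day | Pastoral duties | Partly, through role |

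**3. Possible size for a matched contrast, true training effect zero.** Assumption, not in the protocol: nomination and WEMWBS correlate at r within groups of the same gender, role and experience, with r from 0.1 to 0.3. The top 8% on a normal nomination score lie φ(z)/0.08 = 1.858 SD above the mean. A control teacher matched only on the three variables has, on average, a mean nomination score.

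- Bias for peer supporters = r × 1.858 × 8.4: 1.56 at r = 0.1, 3.12 at r = 0.2, 4.68 at r = 0.3, and 0 at r = 0.
- Pooled bias = that figure × the share of trainees who are peer supporters, taking the selection bias for 1-day trainees as zero. As an approximation, apply 8% to the roughly 60 teachers per school in Study population: 0.08 × 60 = 4.8 peer supporters.
- 1-day course at its 8% minimum: share 4.8 / (4.8 + 4.8) = 0.50, so bias 0.78 to 2.34.
- 1-day course at 16 per school: share 4.8 / (4.8 + 16) = 0.231, so bias 0.36 to 1.08.

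**4. Matching against instrumental variable.** A simulation of 1,500 trials used 12 schools of 60 per arm, ICC 0.02, r = 0.2, five nominees and five other trainees per intervention school, and zero true effect.

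- Matched contrast: mean +1.35 points, SD across trials 1.17.
- Instrumental variable estimate (arm difference divided by proportion trained): mean −0.01, SD 3.99.

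Nomination biases the first and not the second.

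**5. Where the instrumental variable analysis is weak.** Untrained teachers in intervention schools also get the awareness session and can use the peer support service, which strains the exclusion restriction. If they gain d points (assumed 0.25 to 1) and a proportion p is trained, the estimate is off by d × (1 − p) / p.

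- p = 0.16: 1.31 to 5.25 points.
- p = 20.8 / 60 = 0.347: 0.47 to 1.88 points.

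**The case against.** The strongest reply is that the protocol names instrumental variable analysis as one of its two options. That method takes its contrast from randomisation, needs no matched controls and is not biased by nomination, as the simulation shows. A reader might infer from the matching clause that selection will be read as a training effect whatever is done. The document does not support that. What remains is that the clause describing counterparts found by matching does not fit an instrumental variable analysis, and the choice between the two methods is left open. If matching, or principal stratification resting on those variables, is used, the problem applies.

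A reader might also infer that the two courses are pooled. That is the natural reading, because the section speaks of a single training and Table 3 uses the same term for both groups, but no sentence says so. Table 3 and the Reach section elsewhere list peer supporters and 1-day attendees as separate groups. If only the 1-day course is meant, the nomination problem falls away, but the text would have to say so.

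It can also be said that an article leaves the full covariate list to an analysis plan. That is fair for the outcome model. The variables that identify the counterparts, however, are stated here, and nomination is not among them.

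Finally, this is a process-evaluation analysis in cautious wording. That is true, and it limits the consequence.

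**Conclusion.** The point holds conditionally. If the control counterparts of peer supporters are identified by matching, or by principal stratification on gender, role and experience alone, selection by nomination is uncontrolled and could be read as a training effect. The 1-day course is less exposed, because matching on role partly covers pastoral duty. A true instrumental variable analysis escapes this bias and carries the exclusion-restriction problem instead.

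The protocol fixes neither the size nor the direction. A reader might take a bias of several WEMWBS points as established. It is not: the ranges of about 1.6 to 4.7 points for peer supporters alone and 0.4 to 2.3 if the courses are pooled follow from an assumed positive correlation of 0.1 to 0.3, and the bias vanishes at zero correlation. The 3-point target belongs to the primary comparison and serves here only as a sense of scale. The primary result is not affected.

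**What to change.** 1. Analyse the 2-day peer supporter course and the 1-day course separately, each with its own account of who would have been trained.
2. For any matched or principal stratification analysis, add to gender, role and experience the measures already taken before allocation: baseline WEMWBS and PHQ-8 (Table 2), and help provided and received, for which Mechanisms of change refers to baseline scores. The Randomisation section confirms that allocation follows baseline.
3. State which estimator is used. If it is an instrumental variable analysis, drop the matching clause and discuss the exclusion restriction.
4. For peer supporters, label a matched contrast as observational and make no causal claim, because no nominations are described for control schools.

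Collecting nominations in all 24 schools before allocation would address the gap more directly, but it is more than one added question. Nominators are all staff, while the teacher questionnaire covers teaching staff. Nomination is anonymous, while the questionnaire is followed over time by individual. The exercise could also bring the peer-support idea into control schools.

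The cost of items 1 to 4 is some wording and one further model, with smaller groups, wider intervals and a narrower claim. Choosing the instrumental variable route also costs precision: in the simulation its SD was 3.99 points against 1.17 for matching.
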